### Data collection

Measurement of the HUI3, TQ, THI, HADS, FTQ, TCCL, TCS and a cost questionnaire will take place at four moments during a 12 month period. At baseline (T0) the questionnaires will be completed at the audiological centre in the presence of a research assistant. Three (T1), eight (T2) and twelve (T3) months after baseline the patient will be able to complete the questionnaires at home through the internet. Login codes will be sent to their home address two weeks in advance. If patients are incapable of completing the questionnaire through the internet, a paper version will be provided. Non-responders will receive a telephone call as a reminder to complete the questionnaires. If they do not wish to further participate in the study, the reasons for their withdrawal will be recorded.

### Data-analysis

Intention-to-treat analysis will be performed, including all patients that were originally enrolled in the study, irrespective of whether they completed the therapy. To test the differences between the conditions, mixed multilevel regression analyses will be used with a hierarchical backward elimination method. The analysis will be carried out for the POST treatment assessments (after level 1 and level 2 respectively) and follow-up data of the outcome variables. The independent variables are: PRE measurements of the dependent variable, treatment condition, treatment centre, sociodemographics, tinnitus-related variables, and the interaction variable PRE-measurement*treatment. The treatment condition always remains in the regression model, but the other independent variables will be added to increase the power of the analysis and are subsequently eliminated to keep only the significant ones. At each step of the analysis, tests will be done to check for high co-linearity (VIF>10) and/or outliers (Cook's Distance (Cook D)) and Studentised Residual (Sresid)). If Cook D > 1 the case will be removed from the analysis. If Sresid < -3 or > 3, the case will be removed providing that Cook D of this case is considerably higher than from the other cases. By looking at plots of the relationship between each independent variable and the dependent variable, a possible curvilinear relationship is excluded. The prediction errors will be also checked for normality (zresid). For each dependent variable, the initial regression model includes all independent variables and interaction mentioned above. Non-significant interactions (p > .05) will be deleted from the model. Next, non-significant (p > .10, two-tailed) predictors will be deleted one by one, except the treatment factor that always remains in the model. If a significant interaction is found, the treatment effect will be evaluated within strata defined by the covariate interacting with the treatment.

Based on the results of the intention-to-treat analysis, additional per protocol analysis will be performed, incorporating only those patients that completed the therapy. The same analyses as according to the intention-to-treat principle will be performed with respect to the primary outcomes.

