### Patient allocation and randomization

Research information in written format and a declaration of willingness to participate in the trial will be sent to all new patients of the Tinnitus Centre Limburg that are registered with subjective tinnitus complaints. If a patient declares that he or she is willing to participate in the study they will be invited for the baseline measurement. This face-to-face contact will be used to determine whether the patients understood the information correctly and a written informed consent will be obtained. If they agree, a hearing test will be performed to determine the level of hearing loss and the patients are asked to fill in the tinnitus questionnaire (TQ) [15] to determine the severity of the tinnitus. Based on the Fletcher Index and the scores on the TQ the patient will be randomly assigned to one of the treatment groups. Since treatment depends on tinnitus severity and the severity of hearing loss it will be important that these two prognostic factors are equally presented in the UC group and the TCL group.

Treatment allocation will be achieved by block randomisation (four blocks; A, B, C & D) to ensure equal and balanced groups. A randomization list was generated using randomization software. An equal number of patients will be allocated to the TCL group and the UC group. Patients with a score equal to or less than 46 on the TQ and a Fletcher Index below 60 dB will be allocated to block A. Patients with a score equal too or less than 46 on the TQ and a Fletcher Index equal to or above 60 dB will be allocated to block B. Patients with a score above 46 on the TQ and a Fletcher Index below 60 dB will be allocated to block C. Finally, patients with a score equal to or below 46 on the TQ and a Fletcher Index above or equal to 60 dB will be allocated to block D. The randomization procedure will be performed by an independent person at a location outside TCL.

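### Only treatment is protected from backward elimination, so the primary HUI3 model is chosen from the outcome data and neither stratification factor is guaranteed a place in it

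*Protocol article*

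**What the plan says.** The Data-analysis section lists the candidate terms: "The independent variables are: PRE measurements of the dependent variable, treatment condition, treatment centre, sociodemographics, tinnitus-related variables", plus the interaction of the baseline value with treatment. It then fixes the model-building rule:

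- Starting point: "For each dependent variable, the initial regression model includes all independent variables and interaction mentioned above".
- Interactions: "Non-significant interactions (p > .05) will be deleted from the model".
- Main effects: "Next, non-significant (p > .10, two-tailed) predictors will be deleted one by one, except the treatment factor that always remains in the model".
- If the interaction survives: "If a significant interaction is found, the treatment effect will be evaluated within strata defined by the covariate interacting with the treatment".

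The purpose given for the covariates is power, after which they are kept only if significant: "the other independent variables will be added to increase the power of the analysis and are subsequently eliminated to keep only the significant ones".

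The section on patient allocation and randomization sets the strata by TQ (cut at 46) and Fletcher Index (cut at 60 dB), and says of them that "it will be important that these two prognostic factors are equally presented in the UC group and the TCL group". The Discussion, under Design, presents the stratified randomisation as a strength. No section states a separate, fixed model for HUI3.

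**The concern.** A primary analysis should be settled before the outcome is seen and should reflect how patients were randomised. Here the outcome data decide which covariates remain. The final standard error is computed as if that set had been fixed in advance, which tends to make p-values slightly too small. The two factors that the design balances, because they are thought prognostic, have no reserved place. The selection is run afresh for each dependent variable, so the adjustment set may differ between outcomes.

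At stake are the pre-specification of the primary test and a small excess of false positives.

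**Working it through.** **The plan's own figure.** The sample size section uses a difference of 0.065, SD 0.15, two-sided 5% and 80% power. Then n per group = 2 × (1.960 + 0.842)² × (0.15/0.065)² = 83.6, so 84 (85 with the t distribution), against 86 stated. This reproduces closely enough, and the point does not rest on it. Two analysable totals are used below: 198 × 0.85 ≈ 168, and 2 × 86 = 172.

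**How often would a factor be deleted?** Let r be the partial correlation with the outcome (assumed, since the protocol gives none), with 168 patients and two other terms in the model. Put z = atanh(r) × √(168 − 3 − 2). Then P(p > .10) ≈ Φ(1.645 − z) − Φ(−1.645 − z). If such a factor is omitted, the residual SD grows by the factor 1/√(1 − r²).

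| r | P(deleted) | Growth in residual SD |
|---|---|---|
| 0.05 | 0.83 | 0.1% |
| 0.10 | 0.64 | 0.5% |
| 0.15 | 0.39 | 1.1% |
| 0.20 | 0.17 | 2.1% |

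Deletion is likely for a weak factor, but a weak factor costs little when it goes.

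**Type I error, first simulation.** 84 per arm, no treatment effect, baseline correlation 0.6, four weak prognostic factors plus noise variables, 8,000 trials per setting. With 10, 15 and 20 candidates, backward elimination rejected in 5.75%, 5.59% and 5.73%. A fixed model with three covariates rejected in 5.24%, 4.95% and 4.58%. Monte Carlo standard error is about 0.25 points.

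**Type I error, second simulation.** 172 patients, 1:1 randomisation within strata, eight pure-noise covariates, least squares at one time point, 4,000–6,000 trials per setting. The stated rule was applied: interaction out at p > .05, then main effects out one at a time at p > .10, treatment always kept, and baseline kept if its interaction stays. The comparator is treatment + baseline + both strata. Coefficients are standardised and assumed.

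| Baseline / TQ / Fletcher | Fixed | Selected | TQ dropped | Fletcher dropped | Baseline dropped |
|---|---|---|---|---|---|
| 0.7 / 0.15 / 0.10 | 5.2% | 5.4% | 40% | 68% | 0% |
| 0.5 / 0.10 / 0.05 | 5.4% | 5.8% | 73% | 86% | 0% |
| 0.3 / 0.30 / 0.20 | 4.8% | 5.4% | 11% | 42% | 0.1% |
| 0.5 / 0 / 0 | 4.8% | 5.6% | 90% | 90% | 0% |
| 0.15 / 0.10 / 0.05 | 4.8% | 5.3% | 74% | 85% | 25% |

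Monte Carlo standard error is about 0.3 points. In these five settings the mean reported standard error after selection was 1–3% below the true spread of the estimates (for example 0.1305 against 0.1350 in the second row).

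**Power.** At an assumed effect of 0.3 SD, with the coefficients of the second row: fixed model 63%, selected model 63%, unadjusted comparison 48%.

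**The case against.** The strongest reply is that little is lost. The rule discards only variables that explain little, and power is the same as for the fixed model. The two influences on the standard error also work against each other. Ignoring prognostic strata makes the test conservative (the unadjusted comparison rejected in 3.7–4.8% of null trials in the second simulation), while selection makes it slightly liberal. The net excess is about half a point, and in single settings it is not far above Monte Carlo error. All of this stands, and it sets the weight of the point. It does not justify leaving the primary model to the data, because the fixed model performs at least as well.

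Several stronger readings are tempting but not supported:

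- *Baseline HUI3 will be lost.* The text permits it, but it hardly ever happened at coefficients of 0.3–0.7. It reached 25% only at 0.15.
- *Hearing loss is excluded from the model.* It is not named, but the article lists categories of covariate and may leave their members to a fuller document. What can be said is that the factor has no guaranteed place.
- *Different covariate sets make the treatment effects incomparable.* In a randomised trial analysed by linear regression without an interaction, different sets target the same mean difference.
- *The inflation is nearer 7%.* When a significant interaction replaced the overall test by tests in two baseline strata, the simulation gave 6.6–7.6%. That comes from the interaction step and from an assumed median split, which the protocol does not specify. It does not measure covariate selection.

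Nor can the point be set aside as detail left to an analysis plan. The article states the rule, with thresholds, and a plan that fixed the model would contradict it.

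**Conclusion.** The point holds as a matter of pre-specification and of matching the analysis to the stratified design. The stated rule lets the HUI3 data choose the primary covariates and does not secure the stratification factors. The size is modest: about 5.3–5.8% type I error with selection against about 4.6–5.4% with a fixed model, and no demonstrated loss of power. These figures rest on assumed covariate strengths, an assumed number of noise candidates, and a single-time-point regression standing in for the mixed model. The change is worth making because it costs nothing in efficiency and removes an avoidable, outcome-driven choice from the primary test.

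**What to change.** 1. State one primary HUI3 model: treatment, baseline HUI3, TQ and Fletcher Index, with time terms, all retained whatever their p-values.
2. Enter TQ and Fletcher Index as continuous variables, or by randomisation stratum. The stratum option must wait until the block definitions are reconciled. In the section on patient allocation and randomization, block D repeats block B (TQ of 46 or less, Fletcher Index of 60 dB or more), and no block covers TQ above 46 with a Fletcher Index of 60 dB or more.
3. Use the same structure for the secondary outcomes. When TQ is itself the outcome, enter it once, as the baseline value.
4. Make backward elimination an exploratory analysis of predictors. Make the baseline-by-treatment interaction exploratory as well, so that the overall treatment effect is always the primary test.

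The cost is a rewording of the analysis section. TQ and the hearing test are obtained before randomisation and HUI3 is measured at baseline, so no new data are needed and the sample size is unaffected.

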### Outcomes and instruments

Primary outcome measure:

· Generic quality of life, as measured with the Health Utilities Index Mark 3 (HUI3) [20]

Secondary outcome measures:

· Anxiety and depression as measured with the Hospital Anxiety and depression Scale (HADS) [21];

· Tinnitus related disability and handicap, as measured with the Tinnitus Handicap Inventory (THI) [22];

· Tinnitus annoyance and severity, as measured with the Tinnitus Questionnaire (TQ) [15];

· Tinnitus-related fear was assessed by the Fear of Tinnitus Questionnaire (FTQ). This novel 17-item questionnaire is based on the Tampa scale for Kinesiophobia [23] and the Pain Anxiety Symptoms Scale [24];

· Dysfunctional beliefs and/or cognitions regarding the tinnitus, as measured with the Tinnitus Coping and Cognition list (TCCL). The TCCL is a recent adaptation of the Pain Coping and Cognition Questionnaire [25];

· Catastrophic (mis)interpretations of tinnitus, as measured with the Tinnitus Catastrophising Scale (TCS). The TCS is a recent adaptation of the Pain Catastrophising Questionnaire [26];

· Costs, as measured with a retrospective cost questionnaire.

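### The intention-to-treat analysis deletes cases on their outcome residual; the Sresid rule has no fixed cut-off and no all-cases analysis is stated

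*Protocol article*

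**What the plan says.** All of this stands in the Data-analysis section of the protocol article.

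- Population: "Intention-to-treat analysis will be performed, including all patients that were originally enrolled in the study, irrespective of whether they completed the therapy".
- Timing of the checks: "At each step of the analysis, tests will be done to check for high co-linearity (VIF>10) and/or outliers", the outlier measures being Cook's distance and the studentised residual.
- Influence rule: "If Cook D > 1 the case will be removed from the analysis".
- Residual rule: "the case will be removed providing that Cook D of this case is considerably higher than from the other cases", for studentised residuals below -3 or above 3.
- Scope: "For each dependent variable, the initial regression model includes all independent variables and interaction mentioned above". HUI3, named as primary under Outcomes and instruments, is one of these dependent variables.

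The only further effectiveness analysis named is a per-protocol one, restricted to patients who completed therapy. It restores no deleted case. The Sample size paragraph of the Discussion says that the number of patients makes most procedures robust to non-normality.

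**The concern.** Residuals and Cook's distance are computed from the outcome measured after randomisation, in a model that always contains treatment. Removing a case because its residual is large is therefore selection on outcome. A patient whose utility truly rises or falls a great deal is a real observation, and may be part of the treatment effect.

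Three things are at stake.

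- The estimate can be biased if large changes are more common in one arm.
- Trimming the tails shrinks the residual variance, so standard errors come out too small even when the arms have the same tails.
- The data analysed can differ between outcomes, assessments and elimination steps, and part of the choice rests on a comparison with no number attached.

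**Working it through.** **Inputs from the protocol article** (Sample size calculation section): difference 0.065, SD 0.15, two-sided alpha 0.05, power 80%, 86 per group before loss to follow-up, 99 per group (198 in total) after it.

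**The plan's own figure.** n per group = 2 × (1.960 + 0.842)² × 0.15² / 0.065² = 83.6, so 84. The t-based value is 85. The stated 86 is within 2 of both. The simulations below use 84 or 86 per arm.

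**Which rule acts.** For a linear model with p parameters and n observations, Cook D = r² × h / ((1 − h) × p), where r is the studentised residual and h the leverage. At average leverage, h = p/n, this is about r²/n.

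- Cook D > 1 with n = 168 needs r of about √168 = 13.
- A patient at 4 SD has Cook D of about 16/168 = 0.10, so the first rule leaves that patient in.
- In simulation Cook D > 1 fired 0 to 0.003 times per trial.
- The bound of 3 on Sresid is within reach. Under normal errors about 168 × 0.0027 = 0.45 cases per model exceed it.

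**Effect of one deletion.** Removing one patient who lies 0.60 (4 × 0.15) from the mean of the others in an arm of 84 moves that arm's mean by 0.60/84 = 0.007, which is 0.007/0.065 = 11% of the planned difference. Several deletions add up only if they fall in the same arm and the same direction.

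**Simulation set-up (assumptions, not document figures).** There were 3,000 trials per scenario in the main runs, with a linear model on treatment and baseline as a stand-in for the mixed model. Deletion ran for one pass or up to four passes, the latter to imitate checking at each step. Where a Cook D condition was applied, considerably higher was taken as more than 5 times the median.

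**Extremes balanced between arms (86 per arm, up to four passes).** With a true effect of 0.065 the mean estimate stayed at 0.065 for every error shape. With no true effect:

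| Errors | Cases removed per trial | Type I error, all data | Type I error, after deletion |
|---|---|---|---|
| Normal | 0.6 | 4.5% | 5.5% |
| t, 4 df | 4.4 | 5.0% | 8.1% |
| Skewed | 7.9 | 5.3% | 8.6% |

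Other runs gave about 6% for normal errors, 6.6% for t(4) with one pass and 6.9% for t(4) with four passes. The range is therefore about 6% for normal errors and 6% to 9% for heavy or skewed errors, depending on the number of passes.

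**Extremes concentrated in one arm (84 per arm, residual SD 0.15, deterioration of 0.60).**

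| Assumed rate, usual care v tinnitus centre | True contrast | One pass | Up to four passes |
|---|---|---|---|
| 5% v 1% | (0.05 − 0.01) × 0.60 = 0.024 | 0.010 | about 0.003 |
| 2% v 1% | (0.02 − 0.01) × 0.60 = 0.006 | about 0.002 | about 0.001 |

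In the 5% v 1% case, four passes also reduced the mean standard error from 0.028 to 0.024. Requiring Cook D above 5, 10 or 20 times the median hardly changed the one-pass result (0.008 to 0.010).

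**Bias in either direction (86 per arm, residual SD 0.13, up to four passes).**

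- If 10% strong responders (gain 0.65) carry a mean effect of 0.065 in the active arm, the estimate falls from 0.065 to 0.002.
- If 5% of the active arm fall by 0.60 and every patient in that arm also gains 0.03, the true mean effect is 0.03 − 0.05 × 0.60 = 0. The estimate moves from 0.001 to 0.030, and rejection rises from 4.9% to 31.9%.

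**The case against.** The strongest reply has four parts.

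**The intention-to-treat sentence is about completing therapy.** It explains itself as "including all patients that were originally enrolled in the study, irrespective of whether they completed the therapy", so outlier handling could be seen as a separate matter. In a repeated-measures model a case may also be one observation rather than one patient. This stands in part: a reader might infer that whole patients are excluded, and the text does not settle that. On either reading, however, genuine outcome data of randomised patients are discarded, and the same section says that all enrolled patients are included.

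**The Cook D > 1 rule is harmless.** This stands as a matter of size. At this sample size the rule is mainly a guard against extreme leverage. It is still unjustified as an automatic deletion, but the quantified harm comes from the Sresid rule.

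**Bias is conditional.** This also stands. With equal tails there is no bias, with near-normal errors fewer than one case per model is removed, and the rates of deterioration used above are chosen rather than documented.

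**The Cook D condition limits the damage.** A reader might take the one-pass result without that condition as an upper bound. It is not one. The tested Cook D conditions gave almost no protection, and repeated passes made the bias larger. A stricter reading of the undefined phrase could remove far fewer cases, so the size is open in both directions.

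A reader might also infer that the person deleting cases knows the treatment arm. The article describes blinding of patients and is silent on the analyst, so that cannot be asserted. The point does not depend on it.

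**Conclusion.** The point holds from the text alone. An analysis declared to include all enrolled patients removes outcome data because of their values, without requiring an error and without an all-cases analysis beside it. The rule that does the work leaves its Cook D comparison undefined. The article's own claim of robustness to non-normality weakens the usual reason for deleting.

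The size depends on the tails. If they are balanced, the treatment estimate is unbiased and the harm is understated standard errors, with type I error of about 6% to 9%. If extremes differ by arm, the estimate is biased, by more than half of the true contrast in both deterioration scenarios examined. These sizes rest on assumed rates, error shapes, numbers of passes and a simplified model. The documents do not support the stronger claim that the trial's estimate will be biased, or by a known amount.

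**What to change.** Remove both deletion rules from the primary and secondary analyses. Keep all observed outcome data of every randomised patient, and correct a value only where a data error has been verified. Use Cook's distance and studentised residuals for diagnosis only. Report a pre-specified sensitivity analysis that either deletes flagged cases, with a numeric cut-off and with case defined as patient or observation, or uses robust or bootstrap standard errors on the full data.

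The cost is a change of wording, one extra analysis and slightly larger standard errors. Design, data collection and the planned 198 patients stay as they are.

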### Sample size calculation and feasibility of recruitment

After attending a specialised tinnitus clinic a change of 0.065 in health state utility as measured with the SF-6D has been observed [9]. To detect this difference (assuming a two-sided significance level = 0.05, power = 80%, standard deviation of the difference = 0.15), 86 persons per group are needed. Taking into account 15% loss to follow up, the required sample size is 99 persons per group (198 persons in total).

Approximately 400 individuals suffering from tinnitus apply to TCL yearly. We expect this number to stay stable or even increase in the coming years. Therefore it is expected that it will not be necessary to actively recruit patients for this trial.

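### No primary HUI3 assessment or contrast is fixed, and a significant baseline-by-treatment term leads to stratum effects, so the single 5% test behind the sample size is not secured.

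*Protocol article*

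**What the plan says.** The section on sample size calculation sets the trial up for one comparison, "assuming a two-sided significance level = 0.05, power = 80%, standard deviation of the difference = 0.15", on an effect taken from "a change of 0.065 in health state utility as measured with the SF-6D has been observed". It concludes that "86 persons per group are needed". No time point is attached to this effect.

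Outcomes and instruments names HUI3 as primary, again without a time point or a summary over time. Data collection measures it at 3 months (T1), 8 months (T2) and 12 months (T3) after baseline.

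Data-analysis then states: "The analysis will be carried out for the POST treatment assessments (after level 1 and level 2 respectively) and follow-up data". The model is a mixed multilevel regression. The one interaction listed is that of the baseline measurement with treatment, and it applies to the primary outcome as to the others: "For each dependent variable, the initial regression model includes all independent variables and interaction mentioned above". It is deleted if p > .05. If it stays, the rule is "If a significant interaction is found, the treatment effect will be evaluated within strata defined by the covariate interacting with the treatment". Treatment itself is never eliminated.

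No section ranks the assessments, defines a contrast pooled over time, gives cut-points for baseline HUI3, or says which result answers research question 1.

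**The concern.** A sample size for one test at 5% protects the error rate only if one test decides. Here up to three assessments can each supply the HUI3 result, and at each one the data decide whether the answer is an overall effect or a set of stratum effects. Each open choice adds a route to a significant finding when the treatment does nothing.

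The strata rule is written into the article, so a later analysis plan would have to override it rather than fill it in. It also makes the main answer depend on a preliminary test, and it sends that answer to subgroups smaller than the trial was sized for. HUI3 is the primary outcome and research question 1 asks for its overall between-arm effect, so the trial's main conclusion is at stake.

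**Working it through.** **Inputs from the protocol article.** Effect 0.065, SD 0.15, two-sided 0.05, power 80%, 86 evaluable per group, 15% loss, 99 per group (sample size section); equal allocation (Patient allocation and randomization); three post-baseline assessments (Data collection); interaction threshold .05 (Data-analysis).

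**Assumptions, because the article gives no figures.** Correlations between HUI3 measurements; strata split at the median of baseline HUI3; the labels after level 1, after level 2 and follow-up correspond to T1, T2 and T3.

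**1. The plan's own figure.** n = 2[σ(z₀.₉₇₅ + z₀.₈₀)/δ]² = 2[0.15 × (1.960 + 0.842)/0.065]² = 83.6, so 84 per group; the t-test version gives 85. The stated 86 is within two patients and gives 81.1% power. A one-sided test would need 66, so the figure belongs to one two-sided 5% test. The 99 is 86 × 1.15 = 98.9. If 15% of 99 are lost, about 84 remain and power is 80.3%. For a single contrast the size is therefore adequate.

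**2. Three separate main-effect tests, any of which may count.** If independent, 1 − 0.95³ = 14.3%. With correlated test statistics:

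| Assumed correlation between tests | 0.3 | 0.5 | 0.7 | 0.8 | 0.9 |
|---|---|---|---|---|---|
| At least one false positive | 13.6% | 12.5% | 11.0% | 9.8% | 8.4% |

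If all four HUI3 measurements share a correlation r, adjustment for baseline leaves (r − r²)/(1 − r²) = r/(1 + r) between the tests. That is 0.23 for r = 0.3 and 0.44 for r = 0.8. Simulated null trials on that basis (86 per arm, 20,000 per setting) gave 12.5-14.0%.

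**3. Strata rule at one assessment.** In the same simulations, when the interaction was falsely significant at least one half-sample stratum was significant about 41-42% of the time. The total is then roughly 0.95 × 0.05 + 0.05 × 0.42 = 4.75% + 2.1% = 6.85%. The simulated values were 6.7-6.9%, against about 5% without the rule.

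**4. Strata rule over three assessments.** The interaction was falsely significant at one or more assessments in about 13% of null trials. The chance of any significant primary result was 17.0-18.8%; the Monte Carlo error is √(0.18 × 0.82/20,000) = 0.3 percentage points. Other correlation structures widen the range. With baseline and residual correlations both 0.6 and 84 per arm (8,000 trials), the results were 11.2% for main effects alone and 15.5% with the rule. Over all settings tried, the range with the rule was about 13-20%.

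**5. One contrast pooled over T1-T3.** Analysis of the mean of the three assessments, adjusted for baseline (84 per arm, 4,000 null trials per setting), gave 4.5-5.0% for the main effect and 6.7-7.0% with the strata rule.

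**6. Consequences for power.** A half-sample stratum with 43 per arm has about 52% power for 0.065. Keeping all three assessments primary at 0.05/3 would need 112 evaluable per group, or 112/0.85 = 132 per group (264 in total) after loss. At 86 per group, power per assessment at that level is 67.3%.

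Backward elimination of covariates and removal of outliers were not simulated.

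**The case against.** The strongest reply is that a mixed multilevel model may yield a single treatment coefficient over all assessments. There would then be no threefold testing, and the 8-20% figures would not apply. This stands as a possible reading. But Data-analysis defines no such pooled contrast, and even under this reading the strata rule leaves about 7%.

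A second reply is that the article nowhere says that any significant assessment or stratum counts as success. That is also true. The larger figures are conditional on it. The weakness is that nothing rules it out.

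Third, the interaction is prespecified, with a stated threshold. Calling the strata post hoc would go too far; what is missing is the cut-points and the standing of the overall effect. The 41-42% in step 3 likewise applies only to the roughly 5% of null trials in which the interaction is triggered at a given assessment.

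Two stronger readings are tempting and should be resisted:

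- **That stratum effects replace the overall effect.** The text says that the effect will be evaluated within strata and keeps treatment in the model. It does not say that the overall effect is withheld.
- **That a pooled model without time terms dilutes the effect by averaging in T1.** The article gives no effect at T1 from which to compute a dilution. The Intervention section expects the first level to suffice for mild complaints, so for those patients T1 does not precede a fuller programme. This charge also needs one pooled fit, whereas the multiplicity figures need separate tests. Both cannot be held against the same analysis.

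**Conclusion.** The point holds in this form: the article plans one 5% comparison, fixes neither the assessment nor the contrast for it, and states a data-dependent route to stratum effects without cut-points and without saying that the overall effect remains primary.

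The size depends on the reading. With separate tests of which any may count, the false-positive chance is about 8-15% for main effects and about 13-20% with the strata rule. With one single-assessment or pooled contrast, the strata rule alone gives about 6-7%. These are ranges under assumed correlations and a median split. Following the stated strata rule exceeded 5% in every setting tried and under either reading. With one fixed contrast and no strata branch, the error rate is about 5% and the planned size stands.

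**What to change.** Name one primary contrast. One option is the difference between TCL and usual care in HUI3 at 12 months, estimated from a baseline-adjusted repeated-measures model with time and treatment-by-time terms. A prespecified average over T1-T3 would also hold the 5% level. The choice should follow the question, since the economic evaluation uses QALYs accumulated over the year and does not by itself dictate month 12. Make the other assessments secondary.

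State that the overall treatment effect, from a model without the baseline-by-treatment term, is always reported as the primary result. Report that interaction only as a secondary effect-modification analysis, with baseline HUI3 kept continuous.

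This changes wording only, and with one contrast the stated 86 evaluable per group gives 81.1% power. The price is that an effect seen only at another assessment or in a subgroup becomes secondary. If all three assessments are to stay primary, the sample size must be revisited (step 6 of the working).
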